### Outcomes

All outcomes will be collected online. Basic demographic data (age, gender, and academic level) will be collected at baseline (T0). Change in perceived stress, the primary outcome, will be assessed using the difference score of the stress scale of the German version of the DASS-21 [40], measured at baseline (T0) and at 1-week follow-up (T2). The stress scale of the DASS-21 consists of 7 items rated on a 4-point Likert scale (0 = “did not apply to me at all” to 3 = “applied to me very much or most of the time”), yielding total scores from 0 to 21 for the difference score. Higher difference scores indicate greater reduction in perceived stress.

The secondary outcomes are the change in depressive symptoms and anxiety. Change in depressive symptoms and anxiety will be assessed using the difference score of the respective DASS-21 scales, measured at T0 and T2. Each scale consists of seven items, which are rated on the same 4-point Likert scale as the stress scale (total difference score range: 0‐21). The additional exploratory outcome, self-compassion, will be measured using the short version of the German Self-Compassion Scale (SCS-D-KF) [41]. This scale comprises 12 items covering 6 dimensions of self-compassion. Each item is rated on a 5-point Likert scale (1=“almost never” to 5=“almost always”). The scale will be administered at T0, T1, and T2. The primary predictor variable is group allocation (intervention vs. waitlist control), which is assigned through randomization and coded dichotomously (0=control, 1=intervention). No data monitoring committee has been established due to the minimal-risk, single-session, fully automated nature of the intervention. Oversight will be provided by the principal investigators.

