### Statistical Methods

Analyses will follow a complete-case per-protocol (CC-PP) approach, including only participants who completed T0, T1, and T2 (complete cases). Inclusion and exclusion criteria for PP are prespecified in the protocol. Linear models in combination with type II ANOVA will be applied to investigate group differences for the primary and secondary outcomes.

The primary outcome is the change in perceived stress (DASS-21 stress scale) from baseline (T0) to 1-week follow-up (T2). Secondary outcomes are (1) change in depression (DASS-21 depression scale) from T0 to T2, and (2) change in anxiety (DASS-21 anxiety scale) from T0 to T2. Group allocation (intervention vs waitlist control) will be included as a between-subject factor.

For the additional outcome self-compassion (SCS-D-KF) (3), which is assessed at T0, T1, and T2, a linear mixed-effects model will be used, including visit (T1 and T2) as a within-subject factor and group as a between-subject factor. Subject ID will be included as a random effect to account for within-subject correlations across visits. Baseline self-compassion (T0) will be included as a covariate to adjust for individual differences at study entry.

Covariates (sex, age, and academic level) will be entered as main effects and as 2-way interactions with group. Nonsignificant interaction terms will be removed from the final model. If significant interactions are detected, post hoc tests will be conducted to explore and describe the effects.

Group differences in change scores of the Visual Analogue Scale stress from T0 to directly after the intervention will be analyzed as a manipulation check to assess whether the intervention produced the expected immediate effect on perceived stress.

Results will be reported as mean (SDs) for the intervention and control groups, 2-sided *P* values, and adjusted between-group differences with 95% CIs. For the secondary outcomes, the significance level will be adjusted using a Bonferroni correction for the number of independent tests. Effect sizes will be expressed as Cohen *d*, derived from the *t* values of the models and adjusted for covariates. By convention, *d*=0.2 will be interpreted as a small effect, *d*=0.5 as a medium effect, and *d*=0.8 as a large effect.

All analyses will be performed using R (version 4.5.X; R Development Core Team) [31].

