### Attrition and Assessment of Potential Bias Under the CC-PP Approach

As the primary analyses follow a CC-PP approach requiring observed data at T0, T1, and T2, potential bias due to attrition will be assessed. Completion rates will be summarized by randomized group and compared using chi-square or Fisher exact tests, as appropriate. Baseline characteristics will be compared between completers and noncompleters, prioritizing the corresponding T0 value of each primary and secondary outcome, using appropriate statistical tests and standardized mean differences.

To formally evaluate differential attrition while accounting for baseline outcome severity, dropout will be modeled separately for each outcome using logistic regression with treatment group as the primary predictor, adjusted for the respective outcome’s T0 value as well as age and sex (dropout ~ group+outcome_T0+ age+sex). If the number of dropout events is insufficient to support covariate-adjusted models, parsimonious models will be fitted as prespecified. Sensitivity analyses under an intention-to-treat framework using linear mixed-effects models with all available repeated measures will be conducted to assess the robustness of the per-protocol findings to different assumptions about missing data.

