### Sample Size

We conducted an a priori power analysis for an independent-samples *t* test (2-tailed, *α*=.025, power=0.80, allocation ratio=1). The adjusted significance level reflects our decision to control for 2 independent tests corresponding to the 2 secondary hypotheses. Assuming a medium effect (Cohen *d*=0.5) for our primary outcome the change in perceived stress, the required total sample size was estimated as n=156 (78 per group; G*Power 3.1.9.6). Only participants who successfully pass screening will be counted toward the target sample size. Recruitment will be considered complete once 86 eligible participants per group have passed screening. Accordingly, 86 participants per group will be randomized. Assuming an expected attrition rate of 10% per group, we anticipate a final sample of 156 participants, with 78 participants in each group. Since SSIs are generally expected to yield effects in the small-to-medium range, with the strongest effects observed immediately after the intervention and up to 2 weeks later [26], a moderate effect size was deemed the most appropriate estimate.

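### The DASS-21 change-score models omit the outcome's own baseline, a modest and avoidable loss of precision in the primary and secondary comparisons

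*Protocol article*

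**What the plan says.** All references are to the Protocol article.

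- **Outcomes.** Change in stress, the primary outcome, "will be assessed using the difference score of the stress scale of the German version of the DASS-21", taken at T0 and T2. Depression and anxiety are handled the same way: change "will be assessed using the difference score of the respective DASS-21 scales, measured at T0 and T2".
- **Statistical Methods, DASS-21 outcomes.** "Linear models in combination with type II ANOVA will be applied to investigate group differences for the primary and secondary outcomes". The group term is given as "Group allocation (intervention vs waitlist control) will be included as a between-subject factor". The covariate list is explicit: "Covariates (sex, age, and academic level) will be entered as main effects and as 2-way interactions with group". No DASS-21 T0 score is on it.
- **Statistical Methods, self-compassion.** "Baseline self-compassion (T0) will be included as a covariate to adjust for individual differences at study entry".
- **Attrition and Assessment of Potential Bias Under the CC-PP Approach.** The DASS-21 T0 value enters a regression only here, in the dropout model, which is "adjusted for the respective outcome’s T0 value as well as age and sex".
- **Sample Size.** A two-sample t test on the change in stress with d=0.5 ("2-tailed, *α*=.025, power=0.80, allocation ratio=1") gives 78 completers per group, 156 in total.
- **Randomization and Blinding; Recruitment and Eligibility Criteria.** Randomisation is simple, with no blocks or strata. Entry requires a DASS-21 stress score above 7.

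**The concern.** Subtracting T0 from T2 uses the baseline, but with a slope fixed at 1. A linear model with T0 as a covariate estimates that slope. For a seven-item self-report scale measured a week or so apart, a slope below 1 is the ordinary expectation, and the difference score then over-corrects for baseline. This has two consequences:

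- The residual variance is larger than necessary, so confidence intervals are wider and power is lower.
- An arm that happens to start higher shows extra apparent reduction with no treatment effect behind it. Simple randomisation does not limit such an imbalance.

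The omission is stated and is not just left to another document: the covariate list for the DASS-21 models is given in full, and the article names baseline as a covariate where it is wanted (self-compassion, dropout). The precision matters because the Sample Size section expects single-session interventions to have small-to-medium effects but plans for d=0.5.

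**Working it through.** **1. The plan's own figure.** Two-sample t test, noncentral t, d=0.5, two-sided alpha .025, 1:1 allocation. Power is 79.8% at 77 per group and 80.4% at 78, so 78 per group (156) reproduces. At two-sided alpha .05 the same 78 per group give 87.3%. Both levels are shown below: .025 is the planning value, while the Statistical Methods section applies a Bonferroni correction only to the secondary outcomes.

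**2. Variance ratio.** Let b be the slope of T2 on T0, and v the variance of T0 among those enrolled as a share of its variance before the entry cut. With the uncut variances at T0 and T2 equal and scaled to 1, b equals the uncut correlation r, and:

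- residual variance with T0 in the model: 1 − b²
- variance of the difference score: (1 − b²) + (1 − b)²·v
- ratio = (1 − b²) / [(1 − b²) + (1 − b)²·v]

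With no entry cut (v=1) this reduces to (1 + r)/2.

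**3. Effect of the entry cut on stress.** Assumed, because the article gives no figures: latent mean 9, SD 4, scores rounded to 0–21, T0 above 7 retained, r from 0.4 to 0.7. In simulation at r=0.5 the slope is about 0.50 with or without the cut. The SD of T0 falls from 3.96 to 2.68, so v = 2.68²/3.96² = 7.18/15.68 = 0.458.

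**4. Result for stress at 78 per group.** Effective d = 0.5/√ratio; residual df = 156 − 3 = 153; the interval narrows by 1 − √ratio.

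| r | ratio | CI narrower by | power, alpha .05 (87% without T0) | power, alpha .025 (80% without T0) |
|---|---|---|---|---|
| 0.4 | 0.84/(0.84 + 0.36×0.458) = 0.836 | 9% | 92% | 87% |
| 0.5 | 0.75/(0.75 + 0.25×0.458) = 0.868 | 7% | 91% | 86% |
| 0.6 | 0.64/(0.64 + 0.16×0.458) = 0.897 | 5% | 91% | 85% |
| 0.7 | 0.51/(0.51 + 0.09×0.458) = 0.925 | 4% | 90% | 84% |

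Direct simulation gives the same ratios to within 0.003. In completers, the gain equals moving from 156 to between 156/0.925 ≈ 169 and 156/0.836 ≈ 187 under the difference-score analysis.

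**5. Sensitivity to the assumptions.** Over v = 0.4 to 0.6 and b = 0.3 to 0.8 the ratio runs from 0.76 to 0.96, and power at alpha .025 from 91% down to 82%. With latent mean 7, SD 4 and r=0.7 the ratio is 0.944. The gain disappears only as the slope approaches 1.

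**6. Chance imbalance.** The difference-score contrast shifts by (1 − b) times the baseline difference between arms. Under the assumptions above, the standard error of that baseline difference is 2.68 × √(2/78) = 0.43 points. At b=0.5 an imbalance of one standard error moves the estimate by about 0.5 × 0.43 = 0.21 points.

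**7. Not computed.** Depression and anxiety. Depression is cut from above at entry (scores of 10 or more are excluded) and anxiety has no stated cut, so the stress figures do not carry over.

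**The case against.** The strongest reply is that nothing is invalid. Under randomisation the change-score comparison is unbiased, the sample size was set for exactly that outcome, and the power target is met without adjustment. All of this stands, so the point concerns efficiency.

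Four stronger readings are tempting and fail:

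- **That the entry cut makes matters worse.** Selecting on T0 leaves the slope of T2 on T0 unchanged and narrows the spread of T0, so both the gain from adjustment and the typical imbalance shrink. Regression to the mean is expected equally in both arms and does not bias the contrast.
- **That the gain is as large as (1 + r)/2 implies.** At r=0.5 that formula gives 0.75, as if 156 completers were worth 208, and 95% power at alpha .05. It ignores the entry criterion and so does not describe the stress outcome here.
- **That the article contradicts itself.** The self-compassion model has T1 and T2 as responses, so baseline can enter only as a covariate. The DASS-21 response already contains T0 by subtraction. These are two recognised uses of baseline, and the contrast shows only that the authors accept the covariate approach.
- **That the intention-to-treat sensitivity models cure the problem.** They use all available repeated measures, but their handling of baseline is not stated and they are not the primary analysis.

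A registered analysis plan is mentioned and is not shown. It might include T0, but the article's explicit list does not.

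**Conclusion.** The point holds as a modest efficiency improvement that the trial should adopt. The DASS-21 models omit the outcome's own baseline and so give up precision whenever the slope of T2 on T0 is below 1. They also leave the estimate more exposed to chance imbalance than it need be. For stress, the residual variance with adjustment is about 0.84 to 0.93 of that without, which means intervals about 4 to 9% narrower and a power gain at d=0.5 of roughly 2 to 5 points at alpha .05 or 3 to 7 points at alpha .025. These sizes rest on an assumed latent mean, SD and T0–T2 correlation, none of which the article gives. The direction does not depend on them, apart from the one degree of freedom spent. The planned analysis remains valid and the stated 156 is correct. For depression and anxiety the argument is the same, but its size is not established.

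**What to change.** By a dated amendment before analysis, add the respective DASS-21 T0 score as a prespecified main effect in the primary and both secondary models: change ~ group + T0 + sex + age + academic level.

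- **Keep T0 in every model.** State that it is always retained and takes no part in the rule that tests interactions with group and drops the nonsignificant ones.
- **The outcome definition can stay.** If T0 − T2 = a + g·group + c·T0, then T2 = −a − g·group + (1 − c)·T0. The group effect is the same apart from sign, whichever response is used.
- **Report** the baseline-adjusted mean difference with its 95% CI.
- **Align the registered analysis plan** with the article on this point.

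The cost is one degree of freedom per model and an amendment with a registry update. No new data are needed: T0 is already collected and the questionnaires require all items before submission. With 67 enrolled at April 15, 2026, no interim analysis planned and analysis due in winter 2026, the change can still be made in advance of any outcome comparison.

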### Research Objectives and Hypotheses

The primary objective is to evaluate the effectiveness of a compassion-focused online SSI in reducing self-reported stress among university students. The secondary objective is to evaluate the effectiveness of the SSI in reducing depressive symptoms and anxiety. The study will test four hypotheses: (1) The intervention group will show a greater reduction in perceived self-reported stress (DASS-21 stress scale) from baseline to 1-week follow-up than the waitlist control group, (2) the intervention group will show a greater reduction in depressive symptoms (DASS-21 depression scale) than the waitlist control group from baseline to 1-week follow-up, (3) the intervention group will show a greater reduction in symptoms of anxiety (DASS-21 anxiety scale) than the waitlist control group from baseline to 1-week follow-up. Furthermore, we expect that (4) the intervention group will report higher improvements in self-compassion from baseline to postintervention and 1-week follow-up compared to the waitlist control group.

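### The complete-case rule discards observed self-compassion scores that the mixed model planned for hypothesis 4 could use

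*Protocol article*

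**What the plan says.** All references are to the protocol article.

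- **Analysis set.** Statistical Methods opens with a rule for every analysis: "Analyses will follow a complete-case per-protocol (CC-PP) approach, including only participants who completed T0, T1, and T2 (complete cases".
- **Model.** The same section specifies, for self-compassion, that "a linear mixed-effects model will be used, including visit (T1 and T2) as a within-subject factor", with group between subjects and a random effect for the participant. It adds: "Baseline self-compassion (T0) will be included as a covariate to adjust for individual differences at study entry". No exemption from the analysis-set rule is given.
- **Measurement.** Under Outcomes, for self-compassion: "The scale will be administered at T0, T1, and T2". The outcome is labelled additional and exploratory there.
- **Hypothesis.** Research Objectives and Hypotheses lists it as the fourth hypothesis, expecting "higher improvements in self-compassion from baseline to postintervention and 1-week follow-up compared to the waitlist control group".
- **Sensitivity analysis.** The section on attrition and bias plans "Sensitivity analyses under an intention-to-treat framework using linear mixed-effects models with all available repeated measures". It names no outcome and presents these as a check on the per-protocol results.

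**The concern.** Self-compassion is the only outcome to which the article assigns two post-baseline visits in its main model. A mixed model with a subject random effect can use a student seen at only one of them. The analysis-set rule removes that ability. A DASS-21 change from T0 to T2 cannot be computed without T2. A T1 self-compassion score, by contrast, is already recorded and is deleted because of what happens six days later.

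Returning at T2 is a post-randomisation event and may depend on how the student responded at T1. The arms also differ in their reason to return: waitlist students get the intervention only after T2, while the intervention arm already has it (Adherence, Retention, and Discontinuation). The planned dropout regression adjusts for the T0 value, age and sex, but not for T1 response, so it would not show this mechanism.

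At stake are some precision and, under a particular loss pattern, a moderate upward bias in the main estimate for hypothesis 4.

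**Working it through.** **1. The plan's own figures.** Sample Size gives d = 0.5, two-sided alpha 0.025, power 0.80 and 1:1 allocation. The exact t test has power 0.798 at 77 per arm and 0.804 at 78, so 78 per arm (156 in total) is reproduced. That calculation concerns the primary outcome and is used here only for the head counts.

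**2. How many students.** 172 enrolled minus 156 completers is 16, or 16/172 = 9.3%. This is a ceiling for T1 scores discarded through T2 loss; it is reached only if every loss occurs after T1.

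**3. Precision under random loss.** The article gives no SD, visit correlation or dropout timing for self-compassion. Assume unit variance, correlation r between any two visits, T1 complete, and 10% lost at T2 in each arm (86 x 0.9 = 77.4 complete per arm). Given T0, the residual variance at one visit is 1 - r² and the T1-T2 covariance is r - r². For r = 0.7 these are 0.51 and 0.21.

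- T1 contrast, SE = sqrt(2 x 0.51 / n):
  - complete cases, n = 77.4: 0.115
  - all observed, n = 86: 0.109
  - ratio: sqrt(1/0.9) = 1.054
- Pooled over visits: the mean of two visits has variance (0.51 + 0.21)/2 = 0.36.
  - complete cases: information per arm 77.4/0.36 = 215.0, SE = sqrt(2/215.0) = 0.0964
  - all observed: add 8.6/0.51 = 16.9, giving 231.9, SE = sqrt(2/231.9) = 0.0929
  - ratio: sqrt(231.9/215.0) = 1.038

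So the complete-case SE is about 5-6% larger at T1 and 3-4% larger pooled, with no bias.

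**4. Bias under response-related loss.** Simulation with assumed inputs: true effect 0.30 SD at both visits; r from 0.6 to 0.8; all loss after T1; 10% random loss on waitlist; 10% loss in the intervention arm, with log-odds rising by 0.7, 1.0 or 1.5 per SD of poorer T0-T1 change (odds ratios 2.0 to 4.5).

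| Fit | Pooled over visits | T1 contrast (group-by-visit term added) |
|---|---|---|
| Complete cases | 0.33-0.36 | 0.33-0.39 |
| All observed visits | 0.29-0.31 | 0.29-0.31 |

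A separate simulation, with loss driven by the T1 score itself at about 10% base loss, gave 0.33-0.38 for the T1 contrast in completers and 0.30 using everyone seen at T1.

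**5. What the bias depends on.**

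- With the same dependence and the same 10% loss in both arms, the complete-case estimate returns to 0.30.
- If the 10% is split evenly before and after T1, it is 0.32-0.35 at T1 and 0.31-0.33 pooled.
- If intervention loss were 20%, twice the planned rate, it would be 0.38-0.46 at T1 and 0.36-0.41 pooled.

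**The case against.** **The sensitivity analysis may already use these scores.** An all-available-data mixed model is planned, and self-compassion is the outcome it fits best. A reader might infer from the complete-case rule that the T1 scores are lost to the trial; the article does not support that. What remains is that the sensitivity analysis names no outcome and leaves the main estimate complete-case.

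**The outcome is exploratory.** It enters neither the sample size nor the stated alpha adjustment, and the primary and secondary conclusions do not depend on it. This stands and limits the weight, although it is still one of the four hypotheses to be tested.

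**The article states no T1 contrast.** The interactions with group that it names are those with sex, age and academic level. Without a group-by-visit term the model yields one effect pooled over visits. A reader might take the T1 figures as the size of the problem; the pooled 0.33-0.36 is the relevant range for the model as written.

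**The bias scenario is one-sided.** It needs loss related to response, differently by arm, and after T1. Students who discontinue the intervention are classed as dropouts and may leave before T1, with no T1 score to recover. At the planned 10% the T1 bias of 0.03-0.09 SD is below the complete-case standard error of 0.115 (r = 0.7). This stands: the article gives no ground for saying that the effect will be overstated, only that it could be.

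**A narrower reading of the rule.** The attrition section speaks of the primary analyses as complete-case. Statistical Methods is not so limited, and the self-compassion model stands under its rule.

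**Conclusion.** The point holds, at modest weight. As written, the main analysis of hypothesis 4 discards T1 scores of students who miss T2 and T2 scores of students who miss T1, although the chosen model can use both.

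The certain part is a small loss of precision whenever such students exist. The conditional part is an upward bias of about 0.03-0.06 SD pooled, on a true 0.30 SD, if poor T1 responders are lost preferentially in the intervention arm after T1 at the planned 10%. It is smaller if part of the loss precedes T1, and absent if loss is unrelated to response or related equally in both arms. Effect, correlations and loss pattern are assumptions. Fitting all observed visits protects against loss that depends on the observed T0 and T1 scores; it does not protect against loss that depends on unobserved T2 scores.

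**What to change.** In Statistical Methods, exempt self-compassion from the three-visit rule. Make the main analysis of hypothesis 4 the same mixed model fitted to all eligible randomised participants with T0 and at least one of T1 and T2, in their assigned group. Screening failures stay excluded, because Randomization and Blinding provides for randomisation before eligibility is fully verified and for replacement of those who fail. Report the three-visit complete-case fit as the sensitivity analysis.

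The cost is one sentence, with no new data, model or participants. Two small downsides: the number analysed will differ from that for the DASS-21 outcomes, and hypothesis 4 will no longer have the per-protocol set as its main analysis. Analysis is planned for winter 2026, so the change can be made before any data are analysed.

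### Interactions are kept by significance and Cohen d is read from the resulting t values, so d can become a reference-level effect while the type II test still addresses the average effect

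*Protocol article*

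**What the plan says.** Protocol article, Statistical Methods, on the test: "Linear models in combination with type II ANOVA will be applied to investigate group differences for the primary and secondary outcomes". On covariates: "Covariates (sex, age, and academic level) will be entered as main effects and as 2-way interactions with group". The selection rule follows: "Nonsignificant interaction terms will be removed from the final model". If a term survives: "If significant interactions are detected, post hoc tests will be conducted to explore and describe the effects". The report is to give "adjusted between-group differences with 95% CIs", and Cohen d is to be taken from the t "values of the models and adjusted for covariates". The section reads d against 0.2, 0.5 and 0.8 as small, medium and large.

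The Outcomes section says that group is "coded dichotomously (0=control, 1=intervention"). The article does not give the level at which an interaction counts as significant, the coding or centring of the covariates, or the contrast that carries the group effect when an interaction stays. The Sample Size section powers a two-group t test on the change in stress at d=0.5 ("2-tailed, *α*=.025, power=0.80, allocation ratio=1").

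**The concern.** The model behind the primary and secondary estimates is chosen by tests on the trial's own data, and the effect size depends on which model is chosen.

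Take one covariate x: change = b0 + b1·group + b2·x + b3·group·x. The group effect at a given x is b1 + b3·x, and the average effect is b1 + b3·mean(x). If the interaction is dropped, b1 estimates the average effect. If it stays, b1 is the effect at x = 0. For a 0/1 factor that is the reference category. For uncentred age it is age 0, in a trial that enrols ages 18 to 65.

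The type II test of group sets aside the interactions that contain group, so it continues to address an average effect. A single results row could therefore carry a P value for one quantity and a d, and possibly an adjusted difference and CI, for another. The two could visibly disagree.

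**Working it through.** **Plan's own figure.** Two-sample t test, d=0.5, two-sided alpha 0.025, power 0.80: the exact noncentral t gives 78 per group, 156 in total (power 0.804). This matches the Sample Size section, and 156 is used below.

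**How often a null interaction is kept.** Three covariates give three term-level tests per outcome. If there is no true interaction and the tests are independent, P(at least one kept) = 1 − (1 − a)^3, where a is the retention level. The article does not state a, so a range is shown:

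- a = 0.05: 1 − 0.95^3 = 0.143, 1 in 7.0
- a = 0.025: 1 − 0.975^3 = 0.073, 1 in 13.7
- a = 0.10: 1 − 0.90^3 = 0.271, 1 in 3.7

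Simulated trials gave about 13% to 15% at 0.05 and about 6% to 8% at 0.025, depending on the assumed covariate mix.

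**What happens to each statistic.** Simulation of 4,000 trials per setting with 156 completers and no true interaction. Assumptions: sex split 30/70, right-skewed age from 18, three academic levels, reference coding, uncentred age, retention level 0.05, group tested at 0.05 two-sided, d = 2t/√df.

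| Statistic | Rejection, no effect | Rejection, d=0.5 |
|---|---|---|
| Group coefficient t | 0.103 | 0.824 |
| Type II group test | 0.052 | 0.863 |
| Covariate-averaged contrast | 0.052 | 0.863 |
| Main-effects model | 0.052 | 0.861 |

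An interaction was kept in 13.3% of these trials. Under no effect, the group coefficient rejected in 44.3% of them. Check: 0.133 × 0.443 = 0.059, and (0.103 − 0.059)/0.867 = 0.051, so trials without a kept interaction behave normally and the excess comes from the others.

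At a true d of 0.5, among trials that kept an interaction, d from the coefficient had median 0.36 (5th to 95th percentile −0.33 to 0.79). From the covariate-averaged contrast it had median 0.52 (0.24 to 0.79).

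**Dependence on coding.** Further simulations varied the centring (retention level 0.05). The second and third columns are for trials that kept an interaction, at a true d of 0.5. The last column covers all trials under no effect. The ranges reflect different assumed covariate mixes.

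| Coding | d outside 0.2–0.8 | d negative | Type I error of group t |
|---|---|---|---|
| Age uncentred, factors reference coded | 37–44% | 24–28% | 10–11% |
| Age centred, factors reference coded | 24–31% | 5% | 6.5–7.4% |
| All covariates centred | 7% | 0% | 5.0% |

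The main-effects model gave 6% to 7% outside 0.2–0.8 in the same trials, which is sampling error alone.

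**Over all trials.** In the worst coding, 0.14 × 0.44 + 0.86 × 0.07 = 0.062 + 0.060 = 0.122, so about 12% of all trials would report d outside 0.2–0.8. A direct simulation gave 12.6%, against 7.5% for the main-effects model.

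**The case against.** The strongest reply is that the confirmatory test is sound. The article names type II ANOVA for group differences, and that test holds about 5% type I error and 86% to 87% power whether or not an interaction stays. This stands. A reader might infer from the 10% to 11% rejection rate that the primary test is inflated. The documents do not support that, because the rate belongs to a coefficient t test that the article does not name as its test.

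Second, the size rests on choices that the article does not state. The retention level of 0.05 is assumed, and the only numerical alpha given is 0.025. Only group has a stated coding. The phrase on adjusted differences could mean a contrast of adjusted means. With all covariates centred, or with such a contrast, the problem disappears. The largest figures need uncentred age. This also stands, so the claim must be conditional. Centring age alone does not remove the problem, however, because reference-coded sex and level leave 24% to 31% of affected trials outside 0.2–0.8.

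Third, the Trial Design section mentions a registered statistical analysis plan, which may settle coding and contrast. That is possible. But the article itself states both the selection rule and the derivation of d from the model's t values. Together these leave the quantity behind d dependent on the data unless something else overrides them.

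One might also say that most retained interactions would be noise. The documents give no rate of true interactions, so this cannot be claimed. True interactions would make retention more frequent than the figures above.

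**Conclusion.** The point holds in conditional form. The stated rule lets chance interactions decide whether d, and possibly the adjusted difference and CI, refer to the average student or to a reference subgroup. The type II P value is not affected.

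With no true interaction, about 1 trial in 7 per outcome could be affected at an assumed retention level of 0.05, and roughly half as many at 0.025. It would go too far to say that 1 trial in 7 will report a reference-level effect: that also requires reference coding and reading d off the raw group coefficient, neither of which is stated. Where those conditions hold and the true d is 0.5, roughly a quarter to somewhat under a half of affected trials would report d outside 0.2 to 0.8, against about 7% otherwise. The simulated figures also rest on the assumed sex, age and academic-level distributions.

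This is worth correcting because d is the figure the article plans to interpret as small, medium or large.

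**What to change.** Prespecify a model without group-by-covariate interactions for the primary and secondary outcomes, and take the adjusted difference, its 95% CI and d from that model. Fit the interactions in separate models labelled exploratory, which do not alter those results.

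If interactions may stay in the main model, state the retention level, and either centre all covariates or name a covariate-averaged group contrast as the source of the adjusted difference, CI and d.

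In both cases keep d on the change-score scale used in the Sample Size section. Standardising by the baseline SD would move d off that scale, and the entry rule of a stress score above 7 restricts the baseline range.

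The cost is wording only. Moderation is still reported, and the Results section already plans exploratory subgroup analyses. Data analysis is planned for winter 2026, so the change can be made and registered beforehand.
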